### Randomization

The randomization procedure is performed at the end of the inclusion visit, centralized and stratified by center. The 1:1 assignment sequence (based on blocks of four and the use of a computer random-number generator) is produced by the sponsor. The randomization list is not disclosed to the study centers, monitors, statisticians or to the trial team. After collection of the email address of participants, an invitation is sent to each participant to connect to the web-based platform, in order to complete the registration procedure (i.e. to complete the profile and define a login password), as well as fill in the online initial assessments. The intervention group also has access to the personalized electronic lifestyle program whereas the control group not. Due to the nature of the intervention a blind study was not achievable.

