## Methods

### Study setting

ePPOP-ID is an open multicenter randomized controlled trial, which involves 18 university and/or regional hospitals from nine regions in France (study design illustrated in Fig. 1 and Table 1). These centers deliver approximately 30,000 patients per year, which leads to a potential of 2400 to 3000 obese pregnant women per year (i.e. 8 to 10% of the pregnant women being obese), which makes 200 to 250 eligible women per month.

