### Recruitment and eligibility criteria

Screening of participants is performed by midwives and obstetricians of involving hospitals at the first prenatal visit, between 12 and 14 weeks of gestation, at which a verification of inclusion and exclusion criteria is anticipated for the inclusion visit.

To optimize the recruitment, the study was presented to all caregivers that perform visits. Flyers and posters are placed in the waiting rooms of the prenatal consultation area in order to inform potential participants.

Inclusion visit takes place between 12 and 22 weeks. Pregnant women with a singleton pregnancy, a pre-pregnancy BMI between 30 and 40 kg/m^2^, and aged of 18–45 years-old are included. Other eligibility criteria consist of providing written informed consent, having access to internet (by using phone, tablet or computer), being comfortable with the use of internet, and having an email address. Exclusion criteria consist of having a history of more than 2 miscarriages, severe heart disease (arrhythmias, history of myocardial infarction), unstable thyroid disease, uncontrolled hypertension, pre-gestational diabetes, bariatric surgery or any medical condition that may interfere with physical activity during pregnancy, no health insurance, or being legally assisted or unable to consent. Participants can not follow other lifestyle interventions during their participation in the ePPOP-ID trial. The total duration of the trial will be 50 months with an enrolment period of 24 months. The participants are withdrawn of the study if they lose the ability to connect to the program.

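### A single block size of four within each centre of an open-label trial makes up to one third of allocations deducible, which leaves room for selection bias

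*Protocol article*

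**What the plan says.** All references are to the protocol article.

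- Randomization, on timing and strata: "The randomization procedure is performed at the end of the inclusion visit, centralized and stratified by center". Centre is the only stratification factor named, so each centre runs one sequence.
- Randomization, on the sequence: "The 1:1 assignment sequence (based on blocks of four and the use of a computer random-number generator) is produced by the sponsor". One block size is given. Neither variation of the size nor its concealment from sites is described.
- Randomization, on concealment: "The randomization list is not disclosed to the study centers, monitors, statisticians or to the trial team".
- Randomization, on blinding: "Due to the nature of the intervention a blind study was not achievable".
- Recruitment and eligibility criteria, on who recruits: "Screening of participants is performed by midwives and obstetricians of involving hospitals at the first prenatal visit".
- The same section, on timing: "Inclusion visit takes place between 12 and 22 weeks". Its eligibility criteria also include "being comfortable with the use of internet, and having an email address".
- Study setting, on scale: "ePPOP-ID is an open multicenter randomized controlled trial, which involves 18 university and/or regional hospitals from nine regions in France". The Sample size section plans 860 women.

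**The concern.** In a balanced block of four, the last allocation always follows from the first three, and the third follows from the first two whenever those match. Hiding the list protects future entries from being read. It does not stop them from being worked out from past entries, and in an open trial past entries can be known at the site.

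Prediction matters only if a recruiter can act on it. Here there is some room. A woman is screened at about 12 to 14 weeks but may be included at any point up to 22 weeks, so her inclusion can be brought forward or put off. Whether she is at ease with the internet is a judgement. Whom to approach is also decided before randomization.

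At stake is the comparability of the arms. The primary comparison is an unadjusted Chi-square test (Statistics section), which does not correct for a prognostic difference created at enrolment. A larger sample would not reduce such a bias.

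**Working it through.** **Inputs.** Block size 4 and ratio 1:1 (Randomization); 860 women (Sample size); 18 centres (Study setting); 24 months of enrolment (Recruitment and eligibility criteria). The article states no predictability figure, so there is none to reproduce. Its recruitment target is sound: 774 / 0.9 = 860. This point does not change the sample size.

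**Step 1: forced allocations.** A block with two A and two B has 6 orderings.
- AABB and BBAA: the last two allocations are forced.
- ABAB, ABBA, BAAB and BABA: only the last is forced.

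Expected forced allocations per block = (2 × 2 + 4 × 1) / 6 = 1.333, and 1.333 / 4 = 33.3%.

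**Step 2: scale.** 860 / 4 = 215 blocks, and 215 × 1.333 = 287 allocations on average if all blocks are complete. Per centre, 860 / 18 = 48 women, of whom 48 / 3 = 16 are in forced positions.

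**Step 3: best guess.** The observer always names the arm that is behind and guesses at random when the arms are level.
- Position 1: 1/2.
- Position 2: 2/3.
- Position 3: 1/3 × 1 + 2/3 × 1/2 = 2/3.
- Position 4: 1.

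Mean = (1/2 + 2/3 + 2/3 + 1) / 4 = 17/24 = 70.8%.

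**Step 4: alternatives.** Sizes other than 4 are assumptions for illustration. Fixed sizes were enumerated exactly. The mixed schemes were simulated with 48 women per centre, sizes drawn with equal probability, and an observer who knows the possible sizes but not their order.

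| Scheme | Certain | Best guess right |
|---|---|---|
| Fixed 4 | 33.3% | 70.8% |
| Fixed 6 | 25.0% | 68.3% |
| Fixed 8 | 20.0% | 66.6% |
| Random 4 and 6 | about 5.6% | about 69.0% |
| Random 4, 6 and 8 | about 2.1% | about 67.7% |

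Varying the sizes removes nearly all certainty but little of the guessing advantage. The best guess needs only the running balance in the centre: a separate simulation of an observer who follows that balance and knows no block sizes also gave 67.7% for the mix of 4, 6 and 8. Withholding the sizes therefore serves to remove the remaining certainty. It does not remove the guess.

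**Step 5: possible bias (illustration only).** Suppose a share s of forced positions is steered, and the women steered to the two arms differ by 20 percentage points in risk. Neither figure is in the article. Bias = 1/3 × s × 20 points. This is 0.7 points for s = 10%, 2.0 for s = 30% and 3.3 for s = 50%. The planned effect is 50% − 40% = 10 points.

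**The case against.** A reader might infer that recruiters do know one allocation in three. The article does not support that. The figure requires knowledge of the block size, of every earlier allocation in the centre in order, and of where each block begins. The article does not say who at a site learns each result. Screening is spread over midwives and obstetricians, and an average centre randomizes only 860 / 18 / 24 = 2 women a month. Recruiters who do not share results would know less. The block size is printed in the article, but nothing shows that recruiters had it while they enrolled. That it is constant is inferred from the single size given. This part of the objection stands: one third is an upper bound on what can be known.

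The safeguards also count. Randomization is central, comes at the end of the inclusion visit, and uses a withheld list; eligibility is first checked at screening. These steps narrow the room to act, but they leave the deduction from past allocations intact. Such knowledge is also plausible: the professional dashboard (Health care provider's module) shows progress in a programme that only one arm receives.

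A reader might call the bias beyond repair. That is too strong, since history and current pregnancy information are recorded at inclusion and can be adjusted for. What remains is steering on unrecorded impressions. The motivation questionnaire offers limited help, because the initial online assessments follow randomization.

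A reader might also argue that the primary outcome depends strongly on obstetric history visible at screening. The article gives no figure for such a link, so the point does not rest on it.

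**Conclusion.** The point holds as a weakness in design. With one block size of four per centre and open allocation, up to one third of allocations (at most about 287 of 860 on average) can be deduced with certainty, and the best guess is right 70.8% of the time. Both figures assume complete blocks and a fully informed observer. The design allows selection bias; the article does not show that any recruiter predicted or steered an allocation, and that should not be inferred. Analysis can correct for recorded factors only. Because the remedy is cheap, the change is worth making while allocations remain.

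**What to change.** If enrolment is still open, for all allocations not yet used:
- Generate a new list per centre with randomly varying block sizes, for example 4, 6 and 8.
- Withhold the sizes from the sites and from every document that sites receive.

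Certain allocations then fall from 33% to about 2% for an observer who knows the possible sizes, and an observer who does not know them has no firm basis for certainty. The best guess falls only from about 71% to 68%, so sites should also avoid keeping or circulating an ordered record of past allocations.

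The cost is a maximum imbalance per centre of 4 women instead of 2 (half of the largest block), which is tolerable at about 48 women per centre. The list in the central system must be replaced, and part-filled blocks need a rule for closing them. The sample size does not change.

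If enrolment is complete, the list cannot be changed. The sponsor should then report the limitation and add a sensitivity analysis of the primary endpoint adjusted for baseline factors recorded before randomization, with the factors named before database lock. This costs analysis time only.

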#### Health care provider’s module

The professional modules help physicians remotely follow patient’s activities. Professional dashboard includes patient’s details (i.e. inclusion date, validation of profile, completion of questionnaires, self-monitoring of weight, expected date of delivery) and activity of connection (last connection date, progress in the e-learning program). These modules also include administration of the forum and edition of newsletters.

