### Endpoints

The primary endpoint consists of the rate of obstetrical interventions during labor and delivery, defined as caesarean section and instrumental delivery (forceps and vacuum extractor). As secondary endpoints, we include data routinely collected as part of usual antenatal and perinatal care, such as GWG (measured with a scale at each visit), gestational hypertension (defined as systolic blood pressure ≥ 140 mmHg and/or diastolic blood pressure ≥ 90 mmHg after 20 weeks), preeclampsia (defined as gestational hypertension and proteinuria ≥0.30 g/24 h), GDM (diagnosed by a 75 g-oral glucose tolerance test between 24 and 28 weeks according to the guidelines of the International Association of the Diabetes and Pregnancy Study Groups (IADPSG)). Fetal and neonatal collected outcomes, consist of premature birth (defined as birth before 37 weeks), gestational age at birth, birth weight, rate of macrosomia (defined as birth weight > 90th percentile for gestational age), Apgar score, arterial umbilical cord pH, neonatal traumatism, hyperbilirubinemia, respiratory distress syndrome (i.e. needs for oxygen) and transfer in neonatal intensive care unit. Post-natal outcomes are duration of breastfeeding, maternal weight retention and child weight at the postnatal visit (8 ± 2 weeks’ post-partum).

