### Data collection

#### Clinical variables

At inclusion visit between 12 and 22 weeks, demography, medical and family history and current pregnancy health information are collected. Anthropometric variables (weight and height) are measured; blood and urine samples are drawn. No additional follow-up visit is required, as women benefit of the usual care for pregnancy (according to the French guidelines) which consists of 7 prenatal visits and 1 post-natal visit between 6 and 10 weeks after delivery. Information is collected from maternal medical records regarding health during pregnancy including gestational hypertension, preeclampsia and GDM. All women in both groups undergo a 75 g-oral glucose tolerance test (75 g glucose oral load after a fasting period of 10 h minimum) between 24 and 28 weeks. The diagnosis of GDM is made according to the IADPSG criteria (i.e. fasting plasma glucose ≥5.1 mmol/L [0.92 g/L] and/or 1-h glucose ≥10 mmol/L [1.80 g/L] and/or 2-h glucose ≥8.5 mmol/L [1.53 g/L]). The beginning of labor and the delivery mode are collected as well as the occurrence of post-partum hemorrhage. Neonatal and postnatal outcomes include the occurrence of traumatism due to childbirth, Apgar score, umbilical cord pH, admission to neonatal unit and use of phototherapy for hyperbilirubinemia. To address the influence of the intervention on neonatal growth and adiposity, neonatal anthropometric variables (weight, length, adiposity skinfolds) are measured within the first 24 h. At the post-natal visit, maternal demographic data, health since the delivery (post-partum complications such as fever, hemorrhage, thromboembolic events) and duration of breastfeeding are obtained. Maternal anthropometric variables (weight, height) are measured. To address the safety and the impact of the intervention on child health, details regarding the health since birth is also obtained. To address the influence of the intervention on infant adiposity, infant length and weight are measured at birth.

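### The reason given for not blinding covers the women and the programme team, not the clinicians whose decisions form the primary endpoint, and the dashboard can show those clinicians the arm

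*Protocol article*

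**What the plan says.** The Study setting section gives the design: "ePPOP-ID is an open multicenter randomized controlled trial". The Randomization section adds the only reason offered for this: "Due to the nature of the intervention a blind study was not achievable". It does not distinguish between women, programme staff, delivery staff and those who measure outcomes.

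The same section contains the one stated restriction on knowledge of allocation: "The randomization list is not disclosed to the study centers, monitors, statisticians or to the trial team". It also describes how the arms differ. Women in both arms are invited to the platform, register and complete the initial questionnaires, but "The intervention group also has access to the personalized electronic lifestyle program whereas the control group not".

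The Intervention section describes modules for professionals as well as for patients. Under Health care provider's module we read: "The professional modules help physicians remotely follow" the patients' activities. The dashboard lists patient details, including the expected date of delivery, and "activity of connection (last connection date, progress in the e-learning program". The Social network section lets participants write to caregivers under a pseudonym and has caregivers of the team run weekly forum sessions.

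The primary endpoint (Endpoints section) is the "rate of obstetrical interventions during labor and delivery, defined as caesarean section and instrumental delivery (forceps and vacuum extractor". Among the secondary measurements, Clinical variables states that "neonatal anthropometric variables (weight, length, adiposity skinfolds) are measured within the first 24 h", without saying who takes them.

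**The concern.** Delivery mode is recorded with little error, but whether to perform a caesarean section or an instrumental delivery involves clinical judgement. The Background and Discussion sections both state the aim of reducing exactly these interventions, so a clinician who knows the arm also knows the result the trial hopes for. If that knowledge moved the threshold for intervening even slightly, the primary comparison would contain a difference that the programme did not cause. The planned chi-square test compares the two observed rates and cannot tell the two sources apart.

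The intervention is delivered through a website or app used by the woman at home. Nothing about it requires the labour-ward team to know who has it. The single sentence on blinding therefore reaches further than its reason, while another part of the plan opens a route by which the arm can become known to physicians.

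**Working it through.** **1. Who the stated reason covers**

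| Role | Does the nature of the programme force knowledge of the arm? | What the article says about masking |
|---|---|---|
| Women | Yes, they use the programme or do not have it | Open |
| Programme team (content, forum, follow-up) | Yes | Open |
| Clinicians deciding on delivery mode | No | Nothing specific |
| Staff measuring newborn skinfolds | No | Nothing specific |

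**2. What reveals the arm**

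Both arms are on the platform, so being registered or completing questionnaires reveals nothing. E-learning progress is different: only the intervention arm has the programme (Randomization), and progress in it is on the professional dashboard (Health care provider's module). Whoever sees progress recorded for a woman knows her arm. Withholding the list keeps future assignments unpredictable. It does not hide an assignment already made and visible on the dashboard.

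**3. What is not stated**

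The dashboard users are called physicians and the forum staff caregivers of the team. Neither group is identified as managing labour or delivery, and neither is excluded from it.

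**4. Reproducing the plan's own figure**

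Inputs (Sample size section): control rate 50%, intervention rate 40%, two-sided alpha 5%, power 80%, chi-square test.

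n per arm = [1.96 × √(2 × 0.45 × 0.55) + 0.8416 × √(0.50 × 0.50 + 0.40 × 0.60)]² / 0.10² = [1.3790 + 0.5891]² / 0.01 = 387.3

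Rounded up, this is 388 per arm (776); the plan states 387 (774), at which power is 0.7997. Allowance for losses: 774 / 0.90 = 860, as stated. The sample size is sound, and masking the delivery team would not change it.

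**5. Illustration of what a decision-driven shift could do**

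Assumptions, not figures from the article: no true effect, and knowledge of the arm lowers the intervention-arm rate by b on average over all 387 deliveries. Control rate p1 = 0.50, p2 = 0.50 − b, p̄ = (p1 + p2)/2, n = 387.

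- Standard error under the null: se0 = √[2 p̄(1 − p̄)/n]
- Standard error at the shifted rates: se1 = √{[p1(1 − p1) + p2(1 − p2)]/n}
- Probability of a significant result favouring the programme: Φ[(b − 1.96 × se0)/se1]

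For b = 0.02: se0 = √(2 × 0.49 × 0.51/387) = 0.03594; se1 = √[(0.25 + 0.2496)/387] = 0.03593; (0.02 − 0.07044)/0.03593 = −1.404; Φ = 0.080.

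| Assumed shift b | Deliveries in the arm (b × 387) | False significant benefit |
|---|---|---|
| 0 | 0 | 2.5% (nominal) |
| 1 point | 3.9 | 4.6% |
| 2 points | 7.7 | 8.0% |
| 3 points | 11.6 | 13.0% |
| 5 points | 19.4 | 28.5% |

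For scale, the planned difference of 10 points is 38.7 deliveries per arm, and the smallest observed difference reaching two-sided p < 0.05 near a 50% control rate is 28 women (28/387 = 7.2 points).

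**The case against.** The trial calls itself open and does not pretend otherwise. A journal article need not spell out access rights, site instructions or who holds the callipers. The team described under Patient's module (dietician, psychologist, activity coach, midwife, physician) matches the forum topics, so access may already be confined to a central group with no part in deliveries. Messaging is under a pseudonym. Women know their arm and may mention it in labour whatever the protocol says. The sizes of bias are hypothetical, and so is their direction. They are also averages: if only one fifth of delivery teams knew the arm (again an assumption), an overall shift of 2 points would need 2/0.2 = 10 points among those deliveries, and 5 points would need 25.

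Much of this stands, and it rules out several stronger readings that a reader might infer:

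- That delivery staff are given the arm. The article does not say so; it only fails to exclude it.
- That every form of protection is dismissed. The randomization list is withheld from centres, monitors, statisticians and the trial team.
- That caregiver briefing and local screening (Recruitment and eligibility criteria) reveal the arm. Both precede randomization and show only that staff know of the trial.
- That skinfolds are measured by staff who know the arm, or that particular items are missing from the case report form. The measurer is not named and the form is not shown.

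What the objection does not answer is the sentence itself. It states a reason and draws from it a conclusion wider than the reason supports. The pseudonym applies to the social network, whereas the dashboard displays patient details.

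**Conclusion.** The point holds in a limited form. The article rules out blinding for a reason that applies to the women and the programme team but not to the clinicians whose decisions make up the primary endpoint. It also describes a dashboard that reveals the arm to any physician with access, without saying whether those physicians attend deliveries. This is a worthwhile improvement to the design, not evidence that the result will be biased.

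The false-benefit rates of 4.6% to 28.5% are exact consequences of assumed shifts of 1 to 5 points in favour of the programme. A reader might take them as the trial's expected error rate. The documents give no size or direction for such a shift, so they do not support that reading. The figures show only that a shift well below the planned 10 points would matter. The sample size of 774 evaluable and 860 recruited is unaffected.

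**What to change.** Replace the sentence on blinding in the Randomization section with a statement by role:

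- Women and the programme team are not blinded.
- Access to the professional dashboard and to messaging is limited to programme staff who do not manage the labour and delivery of trial participants.
- Allocation is not written in the maternity or labour-ward record.
- Women are asked not to disclose their arm at delivery.
- Newborn skinfolds are measured, where possible, by routine staff who have not been told the arm.

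If access is already restricted in this way, saying so settles that part of the point.

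The change needs a setting of platform access rights and a short instruction to sites. The article gives no costs, but neither item alters the intervention, the endpoint or the number of women. The downside is that masking will be incomplete, because some women will tell staff their arm. The text should say this rather than claim that delivery staff are blinded.
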